## Abstract

**Background:**

Total knee arthroplasty (TKA) is an effective procedure for patients with a variety of knee conditions. The main cause of aseptic TKA failure is implant loosening, which has been linked to poor cement mantle quality. Cementless components were introduced to offer better longer-term biological fixation through osseointegration; however, early designs led to increased rate of revision due to a lack of initial press-fit and bony ingrowth. Newer highly porous metal designs may alleviate this issue but randomised data of fully uncemented TKA (tibial, femoral, patella) is lacking. The aim of the Knee-Fix study is to investigate the long-term implant survival and patient outcomes of fully uncemented compared with cemented fixation in TKA. Our study hypothesis was that uncemented TKA would be as clinically reliable and durable as the gold-standard cemented TKA.

**Methods:**

The Knee-Fix study is a two-arm, single-blinded, non-inferiority randomised controlled trial with 160 patients in each arm and follow-up at 6 weeks, 6 months, 12 months, 24 months, 5 years and 10 years. The primary outcome of interest is implant fixation, which will be measured by assessment of postoperative progressive radiolucencies with the Knee Society Total Knee Arthroplasty Roentgenographic Evaluation and Scoring System. Secondary outcome measures are patient-reported outcomes, measured using Oxford Knee Score (OKS), International Knee Society System (IKSS), Forgotten Joint Score-12 (FJS-12), EuroQol (EQ-5D-5L), VAS Pain, Patient Satisfaction Score and Net Promoter Score.

**Discussion:**

While cemented fixation remains the gold standard, a growing proportion of TKA are now implanted cementless. Highly porous metal cementless components for TKA can offer several benefits including potentially improved biological fixation; however, long-term outcomes need further investigation. This prospective study will help discern long-term differences between the two techniques.

**Trial registration:**

Australian New Zealand Clinical Trials Registry ACTRN12616001624471. Registered trial name: Knee-Fix study (Cemented vs Uncemented Total Knee Replacement). Registered on 24 November 2016.

## Administrative information

Note: the numbers in curly brackets in this protocol refer to SPIRIT checklist item numbers. The order of the items has been modified to group similar items (see http://www.equator-network.org/reporting-guidelines/spirit-2013-statement-defining-standard-protocol-items-for-clinical-trials/).

## Introduction

### Background and rationale {6a}

Total knee arthroplasty (TKA) is an effective procedure for patients with a range of knee conditions, including osteoarthritis, osteonecrosis, rheumatoid arthritis, and arthritis resulting from trauma. This procedure has shown successful outcomes for more than 90% of patients over 20 years [1, 2]. As there is increasing need for TKA, and patient groups are younger with higher expectations of function [3, 4], ensuring implant longevity is important.

The leading cause of aseptic TKA failure is loosening of the implant, which can account for up to 30% of all failures [5, 6]. This mode of failure is linked to poor cement mantle quality and can be identified from the radiographic presence of progressive radiolucent lines [7]. In total hip arthroplasty, the use of cementless components has led to improved fixation and reduced incidence of aseptic loosening, including in younger patients [8]. Therefore, it is anticipated that use of cementless components for TKA may also lower the incidence of loosening and improve implant survival. There are other benefits offered by cementless components, including better bone stock preservation [9], avoidance of cement debris and decreased operating time [10]. In the longer term, the osseointegration provided by cementless components may also outlast cemented fixation, as bone-cement interfaces can wear away over time [11].

The Stryker Triathlon Tritanium® implant that will be used in this study involves complex 3D-printing layering of titanium powder on the surface of baseplates and metal-backed patella [12], creating a highly porous three-dimensional interface. The trabecular titanium coating on the proximal surface of the tibial baseplate is extended to part of the pegs and keels to ensure close contact of the bone-implant interface, allowing for minor inconsistencies with bone resection and morphology. The trabecular titanium metal-backed patella is of a monoblock design. The uncemented implants can also be cemented in situ, which provides the surgeon with intraoperative flexibility once bone quality is assessed. Early reports of the femoral and tibial components of this design show good survivorship in both registry data and peer-reviewed publications [6, 13–15]; however, some studies on previous designs of cementless patella components tend to have higher early revision rates, suggesting a lack of initial press-fit and bony ingrowth [16, 17]. The higher coefficient of friction and rapid ingrowth seen with newer highly porous metal designs may alleviate this issue [11, 18]. Randomised data on fully uncemented (tibial, femoral, patella) in comparison to fully cemented TKA is lacking.

Although cemented fixation remains the gold standard [19], a growing proportion of TKA are now implanted cementless [6, 20]. The aim of the Knee-Fix study is to investigate the long-term implant survival and patient outcomes of fully uncemented compared with cemented fixation in TKA. Our study hypothesis was that uncemented TKA would be as clinically reliable and durable as the gold-standard cemented TKA.

## Objectives {7}

The objectives of the Knee-Fix study are to investigate:If TKA with fully uncemented highly porous metal components are as clinically reliable as TKA with standard cemented components. Outcome measures are health status, functional outcome measures, complications and reoperations.If TKA with fully uncemented highly porous metal components are as durable as TKA with standard cemented components (as judged by survivorship and assessment of progressive radiolucencies).

## Trial design {8}

The Knee-Fix study is a prospective, single-centre, single-blinded, non-inferiority randomised controlled trial. Eligible participants are enrolled into one of two arms: (1) uncemented group: treatment with total knee arthroplasty using a Stryker Triathlon cementless implant with cementless patellar resurfacing, or (2) cemented group: treatment with total knee arthroplasty using a Stryker Triathlon cemented implant with cemented patellar resurfacing.

## Methods: participants, interventions and outcomes

### Study setting {9}

The study site is North Shore Hospital, Takapuna, Auckland 0740, New Zealand. All patients will have surgery and inpatient stays at North Shore Hospital or the Elective Surgery Center, Takapuna, Auckland 0740, New Zealand. Recruitment and follow-up will be at North Shore Hospital and/or Waitakere Hospital, Henderson, Auckland 0610, New Zealand.

### Eligibility criteria {10}

#### Inclusion criteria

Patients must (1) be male or non-pregnant female between 40 and 75 years old, (2) be eligible for cruciate retaining knee replacement, (3) have a primary diagnosis of osteoarthritis, (4) have intact collateral ligaments, (5) have signed the study-specific informed consent document and (6) be willing and able to comply with specified pre-operative and post-operative clinical and radiographic evaluations.

#### Exclusion criteria

Patients (1) have had total, unicompartmental reconstruction or fusion of the affected joint; (2) have previous osteotomy around the knee; (3) have a body mass index (BMI) ≥ 41; (4) have a deformity requiring use of stems, wedges or augments with the Triathlon Total Knee System; (5) have a varus/valgus malalignment ≥ 20° (relative to mechanical axis); (6) have a fixed flexion deformity ≥ 20°; (7) have a neuromuscular or neurosensory deficiency; (8) have a systemic or metabolic disorder leading to progressive bone deterioration or poor bone quality; (9) are immunologically suppressed or receiving steroids in excess of normal physiological requirements; (10) have a cognitive impairment, an intellectual disability or a mental illness; (11) are not undergoing patellar resurfacing; or (12) are having simultaneous bilateral TKA.

### Who will take informed consent? {26a}

The investigators or delegated research assistants will carry out informed consent according to Good Clinical Practice (GCP). This includes informing potential candidates about the purpose and duration of the study, as well as explaining study-specific evaluations, risks and potential benefits that may result from being in the study. Participants are free to refuse participation, decline or withdraw from the study at any time without compromising their medical care. Participants will be given time to read, understand and, if agreeable, sign the study-specific Participant Consent Form prior to study enrolment.

### Additional consent provisions for collection and use of participant data and biological specimens {26b}

Biological specimens are not collected for this study and collection of participant data is incorporated into the consent process for participation listed in “Who will take informed consent? {26a}” section.

### Interventions

#### Explanation for the choice of comparators {6b}

While cemented fixation remains the gold standard for TKA, the optimal mode of fixation is still debatable. Research comparing the outcomes of cementless vs cemented TKA shows contrasting results [21–23]. In recent years, the use of cementless components has been proposed to offer better biological fixation and improved survivorship due to the improved design features [6, 14, 15]. This prospective randomised controlled trial will help discern long-term differences between the two techniques. As uncemented implants can offer some clinical benefits [13], we plan to conduct non-inferiority analyses, that is, use of fully uncemented TKA is considered acceptable if it is not worse than the gold-standard fully cemented TKA.

#### Intervention description {11a}

The seven consultant surgeons participating in the study will each have performed over 100 TKAs, will be experienced with navigation equipment and will have performed at least five cementless cases in a pilot phase before the study begins. Both study groups will receive primary TKA using the Triathlon Primary Total Knee System (all cruciate-retaining) and Stryker PrecisioN Knee Navigation System [24] according to the Triathlon Knee System Surgical Protocol [25]; however, one group will receive cemented implantation and the other group will receive cementless implantation. A tourniquet will be used for cementation in all cases. Patients will be enrolled to one of the two intervention groups at the time of surgery using allocation concealment.

#### Criteria for discontinuing or modifying allocated interventions {11b}

Surgeons may choose to modify interventions intraoperatively if they feel intra-operative findings mean alternative implants are required, such as the use of stems, augments or additional constraint. Additionally, if inadequate primary fixation (press fit) is obtained with uncemented fixation, the surgeon may choose to cement one or more components. These will be recorded as protocol deviations, and both intention-to-treat and per-protocol analyses will be performed.

#### Strategies to improve adherence to interventions {11c}

The research assistant will prepare randomised concealed allocation of intervention using sealed envelopes, which will be assigned to consecutive patients in consecutive order. Patients are blinded to their intervention group throughout the duration of the study, and surgeons will only be unblinded at time of surgery. All participants will be classified as ‘intent to treat’ and those who did not receive the allocated intervention will continue to be followed up for outcome and safety purposes.

#### Relevant concomitant care permitted or prohibited during the trial {11d}

Appropriate post-operative care will be provided according to the preference of the treating physician and all patients will undergo inpatient and outpatient postoperative rehabilitation programmes according to standard of care.

#### Provisions for post-trial care {30}

All participants will receive standard-of-care follow-up and medical advice from their treating physicians after completion of the study. If adverse outcomes occur as a result of study participation, participants will still receive the same appropriate per usual health care practice as those not involved in the study. TKA patients at our institution undergo a rehabilitation programme, including group knee classes, as standard of care. Physiotherapists carrying out rehabilitation are blinded to the study intervention.

### Outcomes {12}

The main reason for TKA failure is aseptic loosening; therefore, the primary outcome of interest is implant fixation, which will be measured by assessment of postoperative progressive radiolucencies. Standard anterior-posterior (AP) and medio-lateral (ML) X-rays of the study limb will be obtained pre-operatively and post-operatively at 6–12 weeks, and 2, 5 and 10 years post-operatively (Table 1). Radiographic assessment will be performed following the Knee Society Total Knee Arthroplasty Roentgenographic Evaluation and Scoring System [26], which will produce a single score for each component. All radiographs will be measured by one investigator to ensure consistency. The score at the 5-year follow-up will be the primary outcome of interest; however, the scores at other follow-ups will also be measured and presented.

**Table 1 Tab1:** Patient evaluation schedule for Knee-Fix study: an RCT evaluating cemented vs. cementless total knee arthroplasty

	Study period						
	Enrolment	Allocation	Post-allocation				Close-out
Timepoint	***−t***_***1***_ (−2 months)	0	***t***_***1***_ (6–12 weeks)	***t***_***2***_ (12 months)	***t***_***3***_ (24 months)	***t***_***4***_ (5 years)	***t***_***5***_ (10 years)
**Enrolment:**							
**Eligibility screen**	X						
**Informed consent**	X						
***Demographics, medical history***	X						
**Allocation**		X					
**Intervention:**							
***Cemented TKA***		X					
***Cementless TKA***		X					
**Assessments:**							
***AP, ML and Skyline X-rays***	X	X	X^a^		X	X	X
***Oxford Knee Score***	X		X	X	X	X	X
***International Knee Society System***	X				X	X	X
***Forgotten Joint Score-12***					X	X	X
***EQ-5D-5L***	X				X	X	X
***VAS Pain***	X		X	X	X	X	X
***Patient Satisfaction score***				X	X	X	X
***Net Promoter Score***				X	X	X	X

*AP* Anterior-posterior, *EQ-5D-5L *Euroqol 5 dimensions, *ML* Medio-lateral, *TKA *total knee arthroplasty, *VAS* Visual analogue scale

^a^6–12 week X-rays only for patients with inadequate immediate post-op images

Secondary outcomes will be measured using validated questionnaires: Oxford Knee Score (OKS) [27], International Knee Society System (IKSS) [28], Forgotten Joint Score-12 (FJS-12) [29], EuroQol (EQ-5D-5L) [30], VAS Pain [31], Patient Satisfaction Score and Net Promoter Score. These questionnaires will provide a quantitative measure of patient pain, function, health and satisfaction. They will be completed by patients preoperatively and at 6–12 weeks, and 1, 2, 5 and 10 years post-operatively (Table 1).

### Participant timeline {13}

The proposed patient evaluation schedule is presented in Table 1.

### Sample size {14}

The main outcome measure is the incidence of radiolucencies using plain X-rays. To calculate sample size, we used a non-inferiority test; that is, the uncemented-fixation technique is acceptable if it is not worse than the standard cemented TKA technique based on the incidence of radiographic lucencies. Power calculations were based on estimates from a previous RCT, where 11% of cemented TKA and 2% of uncemented TKA were found to have progressive radiolucencies [21]. Using a power of 80%, 95% confidence level and a non-inferiority limit of 9%, 150 patients are needed in each group. An additional 10 patients per group (5%) will be recruited to allow for loss to follow-up, bringing the target to 160 patients per group (total of 320 patients). The estimated loss to follow-up of 5% is lower than other studies, however is based on previous experience of minimal loss to follow-up of our RCT patient cohorts [32]. Every individual in New Zealand accessing health systems is assigned a national unique health identifier, which allows for comprehensive capture of patient contact details, clinical notes and radiographs, including those who have moved to a different area.

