## Trial status

Protocol version 1.2, May 2019. The study began recruiting in September 2017. Decision was made to complete recruitment in March 2020 as a result of the unexpected impact of COVID-19 lockdowns on elective surgery volumes. Last patient visit for this 5-year study is anticipated to be in 2025.

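### The 11% and 2% rates given as the basis for 150 per group yield 23 to 29; 150 needs an unstated 11% in both arms and one-sided 5%, and a two-sided 95% interval would then have about 70% power

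*Protocol article*

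**What the plan says.** Section Sample size {14} of the protocol article sets up a non-inferiority comparison on the incidence of radiolucencies: "To calculate sample size, we used a non-inferiority test". It says the power calculations rest on an earlier RCT, "where 11% of cemented TKA and 2% of uncemented TKA were found to have progressive radiolucencies", and concludes: "Using a power of 80%, 95% confidence level and a non-inferiority limit of 9%, 150 patients are needed in each group". Ten more patients per group for loss to follow-up bring the target to 160, the figure repeated in the abstract ("non-inferiority randomised controlled trial with 160 patients in each arm").

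The section does not say which true uncemented rate was assumed in the calculation, or whether the 95% confidence level is one-sided or two-sided. Section Statistical methods for primary and secondary outcomes {20a} compares proportions by Fisher's exact test and sets significance at p<0.05. It gives no side, and it does not mention the 9-point limit or an interval to hold against it.

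**The concern.** A reader who enters the quoted rates into a standard non-inferiority formula does not get 150, or anything near it. So either the number is wrong or it rests on assumptions other than those printed. The difference matters because two quantities decide what the trial can show: the true uncemented rate assumed under the alternative, and the alpha attached to the confidence limit. If 150 was derived at one-sided 5% but non-inferiority is later judged with a two-sided 95% interval, the primary 5-year comparison has less than the stated 80% power. A failure to show non-inferiority could then reflect the choice of interval rather than the implants.

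**Working it through.** **Inputs.** From Sample size {14}: cemented rate 0.11, uncemented rate 0.02, margin 0.09, power 80% (z = 0.8416), 95% confidence (z = 1.645 if one-sided 5%, 1.960 if one-sided 2.5%, that is, a two-sided 95% interval). From Sequence generation {16a}: 1:1 allocation. My assumption: the true uncemented rate is taken as either 2% or 11%, because the text does not fix it.

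**Formula** (unpooled variance, adverse outcome, pc cemented and pt uncemented):

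n per group = (z_alpha + z_beta)² × [pc(1 − pc) + pt(1 − pt)] / [margin − (pt − pc)]²

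**1. Reproducing 150: 11% in both arms, one-sided 5%.**
Variance sum = 2 × 0.11 × 0.89 = 0.1958. Denominator = 0.09² = 0.0081.
n = (1.645 + 0.8416)² × 0.1958 / 0.0081 = 149.4, so 150. This matches the protocol.

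**2. The quoted rates as true rates: 11% and 2%.**
Variance sum = 0.0979 + 0.0196 = 0.1175. Distance to the margin = 0.09 − (0.02 − 0.11) = 0.18; squared, 0.0324.
- One-sided 5%: n = 22.4, so 23.
- One-sided 2.5%: n = 28.5, so 29.

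**3. Equal 11% rates, two-sided 95% interval.**
n = (1.960 + 0.8416)² × 0.1958 / 0.0081 = 189.7, so 190.

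**4. Power at the planned size, equal 11% rates.**
Power = Φ(0.09 / √(0.1958/n) − z_alpha)

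| Evaluable per group | One-sided 5% | Two-sided 95% interval |
|---|---|---|
| 150 | 80.1% | 70.2% |
| 160 | 82.3% | 73.0% |

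Exact binomial enumeration of the Wald interval agrees: at 150, 80.5% and 70.3%; at 160, 82.8% and 73.1%. With the Farrington-Manning restricted variance, power at 150 is 78.0% and 67.1%, and 202 per group are needed with a two-sided 95% interval.

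**5. Other routes to 150 at 80% power.** A superiority comparison of 11% with 2% needs 90 to 138 per group, depending on pooling, continuity correction and sidedness. Non-inferiority with equal rates of 6.5% needs 93 or 118, and with equal rates of 2%, 30 or 38 (one-sided 5% or 2.5%). With equal 11% rates and a continuity correction it needs 172 or 212. Of the variants tried, only step 1 gives 150.

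**The case against.** The strongest reply is that nothing is miscalculated. Equal true rates are a standard planning assumption in non-inferiority designs, and 95% confidence can properly mean one minus a one-sided alpha of 5%. On that reading 150 is exact and the power is 80%. The section says only that the calculation drew on the earlier trial's estimates, not which rate entered where. This stands: 150 should not be called an arithmetic error.

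Three stronger readings are tempting, and the document supports none of them.

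- A reader might infer that the true power is 70% and the stated 80% is false. That needs both a two-sided 95% interval, which the protocol never specifies, and equal 11% rates. If the uncemented rate really were 2%, power at 150 would exceed 99.9% even with a two-sided 95% interval.
- A reader might infer that the 2% is irrelevant and should be deleted. But 11 minus 2 equals the 9-point limit, so the 2% may be where the margin came from. It needs explaining, not removing.
- A reader might infer that early closure cut the power further, from the Trial status section: "Decision was made to complete recruitment in March 2020 as a result of the unexpected impact of COVID-19 lockdowns on elective surgery volumes". That section gives no number randomised and does not say the target was missed, so no loss of power can be derived from it.

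The reply does not remove the mismatch between the printed basis and the printed result. Nor does it settle the sidedness, which neither the sample size section nor the analysis section gives. A separate analysis plan, not shown here, may fix the interval, but the sample size paragraph would still cite rates that do not produce its number.

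**Conclusion.** The point holds as a fault in the stated basis of the sample size, not as a wrong sum. Read as true rates, the printed 11% and 2% give 23 to 29 per group against the stated 150, a five- to six-fold gap (150/29 = 5.2; 150/23 = 6.5). The printed figure corresponds to 11% in both arms with one-sided 5%; this is inferred from an exact match, since the protocol does not say so.

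The consequence for power is conditional. If the 95% level and p<0.05 are applied as a two-sided 95% interval and the true rate is 11% in both arms, power is about 70% at 150 evaluable per group and 73% at 160, and 190 per group would be needed for 80%. Under the one-sided reading the 80% stands. These figures rest on the unpooled normal approximation; the Farrington-Manning alternative is 2 to 3 points lower at 150.

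**What to change.** - In Sample size {14}, state that 150 per group assumes a true rate of 11% in both arms, a 9-point margin, one-sided alpha of 5% and 80% power.
- In the same section, say what role the 2% rate played, for example whether it set the margin.
- In Statistical methods {20a}, make the non-inferiority decision with the matching limit: the upper bound of the two-sided 90% interval for the difference (uncemented minus cemented) against 9 points.
- If a two-sided 95% interval will be used instead, say so in both sections and restate the power as about 70% at 150 evaluable per group under equal 11% rates.

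The cost is wording, and possibly a less favourable stated power. No extra patients are needed. The choice of limit should be fixed before the 5-year primary analysis.
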